### *Outcomes for research question 2: (acceptability measures)*

The proportion of participants who complete at least three of six online modules will be calculated.

The Credibility/Expectancy Questionnaire (CEQ, ) will be administered to adolescents and parents after module 1 when they have been introduced to the treatment rationale.

Client Satisfaction Questionnaire (CSQ,). This questionnaire will be administered to all participants immediately post-treatment.

### *Outcomes for research question 3: (clinical outcomes measures)*

The Revised Child Anxiety and Depression Scale (RCADS, ) will be used to measure symptoms of anxiety and depression. This questionnaire will be administered by a clinician at pre-treatment and by a clinician blinded to treatment allocation immediately post-treatment and at three-month post-treatment.

Childrens' Global Assessment Scale (C-GAS,) will be used to measure global functioning. A clinician will rate global functioning at pre-treatment and by a clinician blinded to treatment allocation immediately post-treatment and at three-month post-treatment.

The Clinical Global Impressions -Severity and Improvement Scale (CGI-S/I,) will be used to measure symptom severity and improvement. A clinician will rate symptom

severity at pre-treatment and a clinician blinded to treatment allocation will rate symptom severity and improvement immediately post-treatment and at three-month post-treatment. Symptom severity and improvement are rated on a single item ranging from 1-7, with higher scores indicating more severe symptoms and lower scores indicating more improvement.

*Outcomes for research question 4 (target mechanism measures)*

The Cognitive Emotion Regulation Questionnaire (CERQ,) will be used to measure emotion regulation strategies. This questionnaire will be administered to adolescents pre-treatment, immediately post-treatment, and at three-month post-treatment.

Perth Alexithymia Questionnaire (PAQ,) will be used to measure alexithymia. This questionnaire will be administered to adolescents pre-treatment, immediately post-treatment, and at three-month post-treatment.

*Other measures:*

Demographic background data: Parents will answer questions about the parental educational level, occupational status, prior treatment history, and information on how the participants got in contact with the study will be registered (e.g., via self-referral or referral from health care).

Adverse events: Participants are asked to report and rate the discomfort of the eventual adverse events caused by their participation in the treatment. These questions will be administered to all participants at post-treatment. Clinicians will also report eventual adverse events during the treatment period.

Therapist time: The total therapist time spent on both reading what adolescents and parents have written in the modules and providing feedback and messaging participants will be calculated.

|                                  | Pre assessment                         | Post module 1 | Post-treatment | 3-months post-treatment |
|----------------------------------|----------------------------------------|---------------|----------------|-------------------------|
| Clinician-rated (blinded) | RCADS                                  |               | RCADS          | RCADS                   |
|                                  | C-GAS                                  |               | C-GAS          | C-GAS                   |
|                                  | CGI-S/I                                |               | CGI-S/I        | CGI-S/I                 |
| Adolescent- rated         | CERQ                                   | CEQ           | CERQ           | CERQ                    |
|                                  | PAQ                                    |               | PAQ            | PAQ                     |
|                                  |                                        |               | CSQ            |                         |
|                                  |                                        |               | ADVERSE EVENTS |                         |
| Parent-rated              | Questions about demographic background | CEQ           | CSQ            |                         |

Table 1: List of measures and time-points

## Safety procedures

During the study period, the adolescents will be under continuous monitoring by the research group. At inclusion, an experienced clinician will assess suicide risk. Patients with acute suicidality will be excluded from the study and receive treatment recommendation and referral if needed. Suicidal ideation will be continuously monitored (weekly during treatment and at post-treatment and three-month post-treatment), ensuring that sudden deterioration in mental health is detected and additional care is provided.

## Handling of Adverse Events

Adverse Event (AE) is defined as: Any untoward medical occurrence in a subject to whom a medicinal product is administered and which does not necessarily have a causal relationship with this treatment.

Serious Adverse Event (SAE) is defined as: Any untoward medical occurrence that at any dose requires inpatient hospitalization or prolongation of existing hospitalization, results in persistent or significant disability or incapacity, is life-threatening, or results in death.

During treatment, AE and SAR are registered by a clinician. All AE that occurs during the trial and which are observed by a clinician or reported by the subject will be registered regardless of whether they are assessed as related to the treatment of not. Assessment of causal relationship, severity, and whether the AE is considered to be an SAE will be made by the project investigator. For each AE/SAE, a

description of the event is recorded, start and stop dates, causal relationship, severity, and whether it is an AE or SAE. Serious Adverse Events (SAE) are reported to the sponsor on a special SAE form within 24 hours of the investigator being informed of the SAE.

## Ethics

The trial will be performed in compliance with this protocol, the Declaration of Helsinki, ICH-GCP (Good Clinical Practice), and current Swedish regulations governing this clinical trial. This study has been approved by the Swedish Ethical Review Authority.

## Statistical analyses

The data will be visually inspected using histograms to check for distribution assumptions and outliers. The analyses will apply intention-to-treat (ITT) method.

Descriptive statistics, independent sample t-test, and binomial test will be used to analyze primary objective and research questions 1-3. Differences between treatments in satisfaction and therapist time will be analyzed using independent sample t-tests. To test whether blind assessors' guesses on treatment allocation differed from chance, a binomial test will be used.

Within group effects will be evaluated in an exploratory manner according to the intention-to-treat principle. Linear-mixed effects regression for continuous outcomes and linear quantile mixed models for ordinal outcomes were fitted for the POET and the Supportive groups separately. These include a random intercept for each participant, and the dummy coded time variable (pre-treatment, post-treatment, and three-month post-treatment, with the pre-treatment time point as reference category. Median effects were estimated, using a linear quantile mixed model using the *lqmm* package in R. P-values and CI were calculated using the bootstrap procedure implemented in the *lqmm* package, with 1000 replications. For CGI-I number of participants classified as responders are presented. Treatment response was defined as a CGI-I rating of 1 (very much improved) or 2 (much improved)

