### Primary objective

Primary objective of this trial is to investigate the feasibility and acceptability of POET relative to an active control treatment.

137 Secondary objective

138 Secondary objectives are to investigate the preliminary effectiveness on clinical  
139 outcomes and target mechanism of POET relative to an active control treatment.

140 Research questions

- 141 1. Are study procedure and design feasible, operationalized as (1) consent rate,  
142 defined as the proportion of eligible participants who consented to inclusion  
143 and randomization; and (2) completion of assessments, defined as completing  
144 at least one clinical outcome immediately post-treatment?
- 145 2. Are POET treatment and the active control treatment acceptable,  
146 operationalized as (1) compliance with the treatments, defined as completing  
147 at least three of six online modules; (2) youth and parent ratings of credibility  
148 and expectancy of treatment after completing the first module; and (3) youth  
149 and parent satisfaction with treatment/course?
- 150 3. Is participation in POET, relative to participation in the active control  
151 treatment, associated with reduction in clinical outcomes, operationalized as  
152 (1) symptoms of anxiety and depression, (2) global functioning, and (3)  
153 symptom severity and improvement, and how large is the effect?
- 154 4. Is participation in POET, relative to participation in the active control  
155 treatment, associated with a reduction in maladaptive emotion regulation  
156 strategies and alexithymia and an increase in adaptive emotion regulation  
157 strategies, and how large is the effect?

158 Time points

159 The primary endpoint of this trial is immediately post-treatment. The secondary  
160 endpoint of this trial is three-month post-treatment.

161 Trial design and procedures

162 Overall trial design

163 This single-blinded, randomized feasibility trial, targeting adolescents with mental  
164 health problems compares POET, an online transdiagnostic emotion regulation  
165 treatment, to an active control treatment. Participants are followed up immediately  
166 post-treatment and three-month post-treatment.

167

168

169

170

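### The secondary objective and research questions 3 and 4 ask for POET's effect relative to the control, but the planned models estimate only change within each arm

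*Protocol*

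**What the plan says.** The secondary objective, in the Protocol's section on aim and objectives, is comparative: "Secondary objectives are to investigate the preliminary effectiveness on clinical" continues as "outcomes and target mechanism of POET relative to an active control treatment". Research questions 3 and 4 open with the same words, "Is participation in POET, relative to participation in the active control". Question 3 goes on "treatment, associated with reduction in clinical outcomes, operationalized as" and lists anxiety and depression symptoms, global functioning, and severity and improvement. Question 4 goes on "treatment, associated with a reduction in maladaptive emotion regulation" and adds adaptive strategies and alexithymia. Both end by asking for the size of the effect.

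The Statistical analyses section evaluates within-group effects, labelled exploratory. Continuous outcomes get linear mixed models, and "linear quantile mixed models for ordinal outcomes were fitted for the POET and the Supportive groups separately". On the model terms it says "These include a random intercept for each participant, and the dummy coded time variable", and no other term is named. CGI-I is presented as numbers of responders.

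The same section also states: "Descriptive statistics, independent sample t-test, and binomial test will be used to analyze primary objective and research questions 1-3". The sentence after it attaches t-tests to satisfaction and therapist time only.

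The Revision history (version 3) records that between-group analysis was taken out and that results are to be shown within each group. Power calculations is likewise framed as pre-post change in each condition.

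**The concern.** The questions are about a difference between randomised arms, and the models estimate change over time inside one arm. Change within an arm combines any treatment effect with everything else that moves scores between assessments, such as natural recovery and regression to the mean. On its own it says nothing about POET relative to supportive treatment.

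The report could then leave its secondary objective and two of its four research questions unanswered. Or it could seem to answer them by setting two columns of within-arm results side by side. Because p-values are planned in each arm for the quantile models, a reader may take a significant change under POET and a non-significant one under control as evidence of superiority. That is not a test of the difference.

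**Working it through.** **1. Questions against analysis**

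| Item | Comparison asked for | Group contrast in Statistical analyses |
|---|---|---|
| Secondary objective | POET against control, clinical outcomes and mechanism | None in the models |
| Question 3 | POET against control, with size | None in the models; CGI-I as responder numbers; a t-test in a joint list, with no clinical outcome named |
| Question 4 | POET against control, with size | None; not in the joint list |

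**2. What the models estimate.** In arm g, the expected outcome at time t is a_g + b_g,t, where b_g,t is the change from pre-treatment. Separate fits give b_POET,t and b_control,t, each with its own uncertainty. The relative effect is b_POET,t − b_control,t. No step of the plan forms it or gives it a CI.

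**3. The stated power.** Inputs from Power calculations and Randomization: N = 30, allocation 1:1, 20% dropout, d = 0.6, alpha .05. This gives 30/2 = 15 per arm and 15 × 0.8 = 12 completers. I assume a paired t-test with d on the change-score SD; sidedness and standardiser are not stated.
- 12 per arm: 47% two-sided, 62% one-sided.
- 15 per arm: 58% two-sided, 71% one-sided.
- 24 completers pooled: 80.4% two-sided.

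The stated 80% is therefore not reproduced per condition under these assumptions. With d on the raw SD, 12 per arm would reach it at a pre-post correlation of about 0.77, which the Protocol does not give. That is a separate matter, so both values are carried forward.

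**4. How often exactly one arm is significant when true change is equal.** The arms are independent, so the probability is 2p(1 − p), with p the power in each arm.
- p = 0.80 (as stated): 2 × 0.80 × 0.20 = 0.32.
- p = 0.580 (15 per arm, two-sided): 2 × 0.580 × 0.420 = 0.487.
- p = 0.475 (12 per arm, two-sided): 2 × 0.475 × 0.525 = 0.499.

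The expression cannot exceed 0.50, so the last value is essentially its ceiling. These figures are per test and illustrate the paired t-test. They do not transfer directly to the three-time-point mixed models or to quantile models with bootstrap inference.

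**5. Precision of a direct contrast.** The approximate 95% CI half-width for a standardised difference, before baseline adjustment, is t(0.975, 2n − 2) × √(2/n).
- n = 15: 2.048 × 0.365 = 0.75 SD.
- n = 12: 2.074 × 0.408 = 0.85 SD.

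Two-sided power for an assumed between-group d = 0.6 is 29% with 12 per arm and 35% with 15. That supports reporting an interval rather than a test.

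**The case against.** The strongest reply is that this was a choice, not an oversight. The Revision history declares it, the power statement is within condition, the analysis is labelled exploratory, and a feasibility trial of 30 has little power for a comparison. All of that stands, and it makes rewording the questions a fully acceptable remedy. It does not remove the conflict, which lies between two current sections: the analysis was changed and the questions were not.

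A second reply is that a reader could subtract one arm's published change from the other's. For the continuous outcomes that would give a rough contrast, but the plan does not provide for it.

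Four stronger readings are tempting, and the text does not support them.
- **Two incompatible analyses for question 3.** The t-test sentence lists three tools jointly for the primary objective and three questions, and the next sentence ties t-tests to satisfaction and therapist time. No clinical outcome, time point or change score is attached. It is loose wording that needs tidying, and it does not supply the missing contrast.
- **The randomised comparison is discarded altogether.** Satisfaction and therapist time are still compared between treatments, and the primary objective does not depend on the models.
- **The report will compare p-values across arms.** Nothing in the plan says so, and CIs are planned. It is a risk of the presentation.
- **The control was included to remove natural recovery and regression to the mean.** The Protocol's stated purpose is to control for non-specific treatment components such as therapist attention and monitoring. The wider list is general methodology.

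**Conclusion.** The mismatch holds on the face of the Protocol and depends on none of the arithmetic. The secondary objective and research questions 3 and 4 ask for a relative effect and its size. The specified models give within-arm change only, and for question 4 no comparative method of any kind is named.

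The calculations only show why within-arm significance cannot stand in for the answer. With equal true change, the arms would disagree on significance in about 32% of trials per test at the stated power, and in about 50% if power is 47%. The second figure assumes a two-sided paired t-test, 12 completers per arm and d on the change-score SD, and should not be quoted without those conditions. The primary feasibility and acceptability objective is not affected.

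**What to change.** Choose one of two routes.

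**(a) Reword.** Restate the secondary objective and questions 3 and 4 as within-arm, descriptive questions. State that no conclusion about POET relative to control will be drawn from the clinical or mechanism outcomes. This keeps the declared analysis decision and costs only wording.

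**(b) Keep the questions and add the contrast.** For each continuous outcome with a pre-treatment value, fit one model to both arms with time, group-by-time, a common pre-treatment mean and a random intercept. For ordinal outcomes with a pre-treatment value, use a corresponding joint quantile mixed model. Report the POET-minus-control difference at post-treatment and three months with a 95% CI, labelled exploratory and without a significance claim. CGI-I has no pre-treatment improvement rating, so report the difference in responder proportions with a CI. The data are already collected, so the cost is one model per outcome, a reversal of the version 3 decision, and visibly wide intervals: about ±0.75 to ±0.85 SD for a standardised difference before baseline adjustment.

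Under either route, limit the independent-samples t-test to satisfaction and therapist time, and take question 3 out of that sentence.

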## Power calculations

30 participants will be included in this study, a sufficient number of participants to answer the research questions about feasibility and acceptability. The sample size (N = 30), given an estimate of 20% dropout, gives a power of 80% to detect a meaningful standardized average difference between pre- and post-measurement in each condition of  $d = 0.6$  given alpha level .05.

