#### Randomization

Eligible participants will be randomly allocated (1:1) to POET treatment or Supportive treatment. Randomization will be conducted by an independent researcher using a true random number service. The random allocation sequence will be placed in opaque sealed envelopes.

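### The stated 80% power for d = 0.6 in each condition holds only for all 24 expected completers together; with about 12 completers per condition it is about 48%

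*Protocol*

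**What the plan says.** Three parts of the protocol bear on this point.

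- **Power calculations.** The total is fixed: "30 participants will be included in this study". Assuming that one in five is lost, the section claims that this total "gives a power of 80% to detect a meaningful standardized average difference between pre- and post-measurement in each condition". The effect size attached to the claim is 0.6 and the significance level is 0.05. The section names no test, sidedness, pre-post correlation or SD for d.
- **Randomization.** "Eligible participants will be randomly allocated (1:1) to POET treatment or Supportive treatment".
- **Statistical analyses.** The mixed models for continuous outcomes and the "linear quantile mixed models for ordinal outcomes were fitted for the POET and the Supportive groups separately". Nothing in the section pools the arms for a pre-post effect.

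Version 3 in the revision history also records that between-group analyses were dropped in favour of within-group results for each arm.

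**The concern.** The power claim is made for each condition, but the sample size and dropout beside it describe the whole trial. With 1:1 allocation a single condition has half of those participants, and the models use each half on its own.

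This is the protocol's only numerical justification of sample size; that 30 is enough for the feasibility and acceptability questions is asserted without a figure. Since version 3, the modelled clinical and mechanism results rest on the per-arm pre-post contrast to which the claim refers. A reader who accepts 80% would put the chance of missing a true d = 0.6 in one arm at 20%. If the claim is wrong, a non-significant change in an arm is much weaker evidence against such an effect than the protocol implies.

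**Working it through.** **Inputs from the protocol**

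- Total N = 30, dropout 20%, d = 0.6, alpha 0.05, target power 80% (Power calculations).
- Allocation 1:1 (Randomization), so an expected 30/2 = 15 per condition.
- Each arm modelled on its own (Statistical analyses).
- Expected completers: 30 × 0.8 = 24 in total, 24/2 = 12 per condition.

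**Assumptions, because the protocol is silent:** two-sided test; d is the mean pre-post change divided by the SD of change. Both are varied below.

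**Formula.** For a paired t-test on n pairs, df = n − 1 and the noncentrality is λ = d√n. Power is the probability that a noncentral t variable with (df, λ) falls beyond ± the 0.975 quantile of the central t with the same df.

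**Step 1: reproduce the stated figure.** With n = 24, λ = 0.6 × √24 = 2.94 and power is 80.4%. With n = 23 it is 78.5%, so 24 is the smallest n that reaches 80%. Inflating for dropout, 24/(1 − 0.20) = 30. Both the N and the power in the protocol are recovered, with all participants as one group.

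**Step 2: power in one condition**

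| Pairs analysed | λ | Two-sided power | One-sided power | d detectable at 80%, two-sided |
|---|---|---|---|---|
| 12 (one condition after dropout) | 0.6 × √12 = 2.08 | 47.5% | 61.9% | 0.89 |
| 15 (one condition, nobody lost) | 0.6 × √15 = 2.32 | 58.0% | 71.4% | 0.78 |
| 24 (both conditions together) | 2.94 | 80.4% | 88.6% | 0.60 |

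At 12 pairs the chance of missing d = 0.6 is 100 − 47.5 = 52.5%.

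**Step 3: other methods at n = 12.** The two-sided normal approximation gives 54.7% and the one-sided 66.8%. Using 22 degrees of freedom, 2 × (12 − 1), as a random-intercept model over three time points might, gives 51.1%. None comes near 80%.

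**Step 4: d scaled by the raw SD.** If the pre and post SDs are equal and the correlation is r, the effect in SD-of-change units is d_z = 0.6/√(2(1 − r)).

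| r | d_z | Two-sided power, n = 12 |
|---|---|---|
| 0.3 | 0.507 | 36.1% |
| 0.5 | 0.600 | 47.5% |
| 0.7 | 0.775 | 68.6% |
| 0.8 | 0.949 | 84.8% |

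For 80% at n = 12, d_z must be 0.8887, so r = 1 − (0.6/0.8887)²/2 = 0.77. One-sided, the required r is 0.69. With all 15 retained it is 0.70 two-sided and 0.61 one-sided, but that sets aside the stated dropout.

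**Step 5: what 80% per condition would take.** 24 completers per arm, hence 24/0.8 = 30 randomised per arm and 60 in total.

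**The case against.** The case for leaving the sentence alone, or treating it lightly, has four parts.

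- **The source of the 80% is inferred.** The protocol does not show its working, so pooling of the arms cannot be proved. This stands, although a match on both 24 completers and 30 enrolled is strong evidence. The shortfall per condition does not depend on how the figure arose.
- **The 48% is conditional.** It assumes a two-sided test and d in SD-of-change units. With raw-SD scaling and a high correlation, 80% is reachable at 12 per arm. This stands as a caveat on the replacement figure. It does not support the sentence as written, because the required correlation of about 0.77 appears nowhere in the protocol.
- **The planned analysis is not a completers' paired t-test.** The protocol specifies intention to treat, random-intercept models on three time points and quantile mixed models for ordinal outcomes. The t-test is therefore an approximation. The variant with 22 degrees of freedom gives 51.1%, and keeping all 15 gives 58.0%, so the conclusion does not change.
- **The consequence is limited.** The primary objective is feasibility and acceptability, the within-group effects are labelled exploratory, CGI-I responder counts are reported as well, and no progression rule depends on significance within an arm. All of this is true. It lowers the stakes without making the 80% correct.

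**Conclusion.** The concern holds. With 30 participants, 1:1 allocation, 20% dropout and separate models per arm, power to detect a pre-post change of d = 0.6 in one condition is about 48%, not 80%. It is 58% if nobody drops out and 62% if the test is one-sided with 12 completers. The effect detectable with 80% power is d = 0.89 at 12 completers, about one and a half times the stated effect (0.89/0.6 = 1.48).

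These figures rest on a paired t-test, d defined by the SD of change, and arms of equal size. The conclusion would reverse only under an assumption that the protocol does not make: raw-SD scaling with a pre-post correlation of about 0.77 or higher (two-sided, 12 completers). The error does not bias any estimate or confidence interval. It overstates what a null result within an arm can show, and it should be corrected.

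**What to change.** Replace the power sentence with one that matches the design, for example:

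> With 15 participants per condition and 20% dropout (12 completers per condition), a two-sided paired t-test at 0.05 has about 48% power to detect a pre-post change of d = 0.6 in SD-of-change units within a condition; the effect detectable with 80% power is d = 0.89. The planned mixed models may differ slightly from this approximation.

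If the 80% is kept, say that it applies to all 30 participants pooled, remove the reference to each condition, and note that no planned pre-post analysis pools the arms. If the calculation in fact used the raw SD and a pre-post correlation, state that correlation and its source. In every case state the sidedness and the SD that defines d, and carry the same wording into the trial report.

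The cost is one sentence in the protocol and one in the report. No more participants are needed and no analysis changes. The stated power becomes less favourable.
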